## Abstract

**Background:**

Patients with traumatic knee complaints regularly consult their general practitioner (GP). MRI might be a valuable diagnostic tool to assist GPs in making appropriate treatment decisions and reducing costs. Therefore, this study will assess the cost-effectiveness of referral to MRI by GPs compared with usual care, in patients with persistent traumatic knee complaints.

**Design and methods:**

This is a multi-centre, open-labelled randomised controlled non-inferiority trial in combination with a concurrent observational cohort study. Eligible patients (aged 18–45 years) have knee complaints due to trauma (or sudden onset) occurring in the preceding 6 months and consulting their GP. Participants are randomised to: 1) an MRI group, i.e. GP referral to MRI, or 2) a usual care group, i.e. no MRI. Primary outcomes are knee-related daily function, medical costs (healthcare use and productivity loss), and quality of life. Secondary outcomes are disability due to knee complaints, severity of knee pain, and patients’ perceived recovery and satisfaction. Outcomes are measured at baseline and at 1.5, 3, 6, 9 and 12 months follow-up. Also collected are data on patient demographics, GPs’ initial working diagnosis, GPs’ preferred management at baseline, and MRI findings.

**Discussion:**

In the Netherlands, the additional diagnostic value and cost-effectiveness of direct access to knee MRI for patients presenting with traumatic knee complaints in general practice is unknown. Although GPs increasingly refer patients to MRI, the Dutch clinical guideline ‘Traumatic knee complaints’ for GPs does not recommend referral to MRI, mainly because the cost-effectiveness is still unknown.

**Trial registration:**

Dutch Trial Registration: NTR3689.

## Background

General practitioners (GPs) are often consulted by patients with traumatic knee complaints. For musculoskeletal disorders, knee complaints are the second most frequent reason (after low back pain) for consulting the GP [1]. Traumatic knee complaints are knee complaints due to a trauma of the knee or are at least of a sudden onset, and therefore likely to be traumatic. Traumatic knee complaints can be caused by e.g. bone bruise, fracture, and/or soft tissue injuries such as lesions of menisci, cruciate ligaments, collateral ligaments and muscles [2-4]. In Dutch general practice, the incidence and prevalence of knee complaints are estimated at 20 and 30 per 1000 persons/year, respectively, whereas the incidence and prevalence of traumatic knee complaints are estimated at 5.3 and 6.8 per 1000 persons/year, respectively [1].

For the GP, diagnosing knee injuries other than fracture or locked knee can be difficult [5-8]. Magnetic resonance imaging (MRI) of the knee can help in establishing the correct diagnosis or in excluding other diagnoses; this additional knowledge can be used to decide on subsequent treatment and/or referral of patients with traumatic knee complaints. MRI is a powerful diagnostic tool for detecting lesions of ligaments, tendons, bone, cartilage and menisci [4,9,10]. MRI showed a sensitivity of 86%, 91%, 76%, a specificity of 95%, 81%, 93% and an accuracy of 93%, 86%, 89% for anterior cruciate ligament, medial and lateral meniscus lesions, respectively [9].

Recommendations for the diagnosis and management of patients with traumatic knee complaints presenting in primary care in the Netherlands are described in the clinical guideline ‘Traumatic knee complaints’ issued by the Dutch College of General Practitioners in 2010 [2]. At the GPs’ initial consultation an urgent referral to a medical specialist is required when there are signs of a fracture, acute locked knee, or severe complaints after patella dislocation [2]. Otherwise, patients are managed conservatively; this generally comprises information and advice about the knee complaints, medication for pain reduction and, if indicated, referral to physical therapy. When complaints have not decreased at follow-up the GP can refer the patient to an orthopaedic surgeon who may request an MRI or perform an arthroscopy or surgery [11]. In the Netherlands, at 1-year follow-up, 57% of patients with traumatic knee complaints had consulted their GP more than once, about one third was referred to physical therapy, and 21% were referred to an orthopaedic surgeon [12].

Direct referral to MRI might be a valuable tool for GPs in making appropriate and informed decisions [13]. Negative MRI findings may enable the GP to reassure patients, treat them conservatively, and avoid unnecessary orthopaedic referrals. Positive MRI findings could confirm the GP’s diagnosis and the decision to either advise conservative treatment or refer to an orthopaedic surgeon in an earlier stage [14].

The DAMASK trial showed that an MRI referral by the GP prior to a provisional orthopaedic appointment yielded significant benefits in patients’ knee-related quality of life when compared with direct referral to an orthopaedic surgeon [15]. Another study showed that early MRI of the knee in patients in secondary care with suspected internal derangement facilitates faster diagnosis at a comparable cost level compared with physical therapy; at 3-months follow-up patients randomised for an early MRI reported significantly less pain, less activity limitations and better patient satisfaction [16].

### Aim

Whether MRI of the knee should enter the diagnostic pathway in primary care, through direct access by GP’s, depends on whether it improves patient outcomes, reduces costs and affects subsequent diagnosis and management. The objectives of this study over a period of 12 months follow-up are:

1. To assess the cost-effectiveness of MRI referral by the general practitioner compared to usual care in patients with persistent traumatic knee complaints.

2. To assess if MRI referral by the general practitioner is noninferior compared to usual care in patients with persistent traumatic knee complaints regarding self-reported knee related daily function.

## Methods

This study has been approved by the Medical Ethics Committee of the Erasmus Medical Centre (Dutch Trial Registration: NTR3689) [17].

### Design

The study will be a multi-centre, parallel group, open-labelled, non-inferiority randomised controlled trial (RCT) with a 1-year follow-up. Figure 1 presents a flow chart of the study.

**Figure 1 F1:**
[figure not shown]
Flow chart of the study.

To assess the generalisability of the findings, patients who are eligible but decline randomisation are invited to participate in the concurrent observational cohort study; in this latter study the inclusion criteria and measurements are identical to those for the randomised patients. Inclusion of these latter patients in an observational cohort will provide insight into the potential selection of patients entering the randomised cohort. Furthermore, it allows to assess the course (e.g. medical consumption and outcomes) of these non-randomised patients presenting with knee complaints after a trauma within the participating general practices, including the frequency of MRI referral and referral to an orthopaedic surgeon.

### Study population

GPs located in the south west area of the Netherlands will recruit eligible patients. The GP informs the patient and sends contact data to the researchers. The researcher contacts the patient by telephone and checks the inclusion/exclusion criteria.

Patients are eligible for inclusion if they (re)consulted their GP with knee complaints (knee pain and/or disability) due to trauma or sudden onset in the preceding 6 months and are aged 18–45 years. Patients are excluded if there is an indication for direct referral to an orthopaedic surgeon (e.g. fracture, acute locked knee, or severe complaints after patella dislocation).

Patients are also excluded when: 1) the knee complaints are already managed in secondary care, 2) the patient is known with osteoarthritis in the affected knee (diagnosis confirmed by a medical specialist), 3) there is other non-traumatic arthropathy (e.g. infection, Reiter’s syndrome, gout, inflammatory bowel disease, or neuropathic pain) or isolated patellofemoral joint pain, 4) there is a previous MRI of the knee within the same episode of knee complaints, 5) there is a previous surgical intervention of the affected knee, or 6) there are contra-indications for MRI (e.g. claustrophobia, metal implants or pregnancy).

### Randomisation and interventions

When patients are eligible for inclusion and have completed the informed consent procedure, the baseline measurement will take place. Hereafter, patients are randomly allocated to the MRI or the usual care group. An independent person produces a randomisation list by computer, using random blocks of 4 and 6. Allocation by one of the researchers ([name] or NS) will be concealed and cannot be influenced or predicted because the randomisation list is not accessible to members of the research team.

#### MRI group

Patients will be referred for an MRI scan of the affected knee at one of the participating MRI centres (in Rotterdam, Amsterdam, Alkmaar, Goes, or Leiden) within 2 weeks after referral. MRI is performed on a 1.5 T system using the ‘acute knee scanning protocol’; this is available in all participating centres and is adjusted for the specific magnetic resonance device. All protocols include imaging in the coronal, sagittal and transversal plans, and all include a T1 and a PD-weighted sequential, with or without fat suppression. All participating musculoskeletal radiologists (n = 12) have adequate experience working with these predefined protocols.

In the Netherlands, there is no standardised way for a radiologist to score and report MRI findings for patients with traumatic knee problems. For this reason, a standardised and a digitalised report was developed for the TACKLE Trial. This report was composed as an online questionnaire, using an open source survey application called the Lime Survey [18]. All radiologists are trained in this standardised scoring of MRI features.

The following items are scored in the MRI report: the quantity of synovial fluid and soft tissues, menisci, anterior and posterior cruciate ligaments, medial and lateral collateral tendons and the bone and cartilage. The report will produce a treatment/referral advice for the GP based on the latest consensus in the literature, expert opinion and daily practice [11,19]. Table 1 presents an overview of the most significant findings and the treatment/referral advice for GPs.

**Table 1 T1:** Types of findings on MRI and related advice

**Positive findings (advice for referral to orthopaedic surgeon)**	**Equivocal findings (advice based on radiologist’s judgement)**	**Negative findings (advice for treatment in primary care)**
Pigmented villonodular synovitis	Synovitis, bursitis, hoffitis, any other cyst	Effusion, Baker’s cyst, ganglion, plica, subcutaneous oedema
	Lesions of the m. quadriceps tendon, the patellar tendon or the patellar retinacula	
Osteochondrosis dissecans fracture	Lesions of the trochlea or patellar alignment anomalies	Bone bruise or bone marrow oedema
Meniscal tears*		Parameniscal cyst, meniscal extrusion, discoid meniscus, isolated lesions of meniscal ligaments or meniscal capsular lesions
Partial or complete anterior or posterior cruciate ligament tears		Mucoid degeneration of the cruciate ligaments
Grade III injury (complete rupture) of the medial collateral ligament or the posterolateral corner		Grade I and II injury of the medial collateral ligament or the posterolateral corner
Grade IV chondromalacia		Grade I to III chondromalacia

*A meniscal tear is defined as an abnormal shape of the meniscus OR as a high signal intensity unequivocally contacting the surface of the meniscus. The latter must be seen on at least 2 adjacent slices in one plane.

The radiologist will report the details on possible pathology to the GP, together with a treatment/referral advice (based on Table 1). In case of positive MRI findings, the advice of the radiologist will be to refer to an orthopaedic surgeon. The orthopaedic surgeon will decide whether arthroscopy or surgery is required, based on clinical findings and on the Dutch orthopaedic guidelines [11,19]. In case of negative MRI findings the advice of the radiologist will be to continue treatment in primary care according to the Dutch clinical guideline ‘Traumatic knee complaints’ (see Usual care group). In case of equivocal findings, based on severity of the injury, the radiologist will decide whether the advice will be to continue treatment in primary care or to refer to an orthopaedic surgeon. Finally, the GP will decide whether or not to refer the patient, based on the radiologist’s report and the patient’s current complaints.

The inter-rater reliability of the radiologist’s advice was determined for eight participating radiologists using 10 MRIs of patients with traumatic knee complaints. The intra-class correlation coefficient was 0.65, reflecting reasonable agreement.

#### Usual care group

These patients are treated according to the Dutch clinical guideline ‘Traumatic knee complaints’, i.e. without MRI [2]. When there are signs of contusion, distortion, medial or lateral collateral ligament lesion, patients are advised to continue their daily activities and load the knee as much as possible. When there are indications of meniscal lesions and/or cruciate ligament lesions, patients are advised to take rest for a few days and to use elbow crutches if necessary. When pain and effusion decreases patients are advised to flex and extend the knee without load bearing, to do isometric muscle training of the quadriceps muscle, and gradually increase their daily activities. For additional support regarding exercises the GP can refer the patient to a physical therapist. Follow-up consultations are planned with an interval of (at most) 2 weeks.

### Outcomes

Patients will fill in questionnaires at baseline and at 1.5, 3, 6, 9 and 12-months follow-up (Table 2). The questionnaires are sent by e-mail which contains a secured hyperlink to the questionnaire. For this purpose the survey application the Lime Survey is used [18].

**Table 2 T2:** Measurement of primary and secondary outcomes

	**Baseline**	**1.5 months**	**3 months**	**6 months**	**9 months**	**12 months**
Primary						
Lysholm	X	X	X	X	X	X
iMCQ/iPCQ	X	--	X	X	X	X
EQ-5D-3 L	X	X	X	X	X	X
Secondary						
KOOS	X	X	X	X	X	X
NRS	X	X	X	X	X	X
GPE	X	X	X	X	X	X
Satisfaction	X	X	X	X	X	X

Lysholm = Lysholm Scale. iMCQ = Medical Consumption Questionnaire from the Institute for Medical Technology Assessment. iPCQ = Productivity Cost Questionnaire from the Institute for Medical Technology Assessment. EQ-5D-3 L = EuroQol 5-Dimensions. KOOS = Knee Injury and Osteoarthritis Outcome Score. NRS = numeric rating scale. GPE = Global Perceived Effect.

#### Primary outcomes

1) Patients’ knee-related daily function is measured with the Lysholm Scale [20]. This scale is well documented according to validity, reliability and responsiveness in patients with traumatic knee injuries [21,22]. The Lysholm Scale summarizes activity limitations and symptoms related to activity. The score consists of 8 items rated on a 100-point scale, with instability and pain being allocated 25 points each [20]. A higher score indicates better knee function.

2) Medical costs are measured for the health care use and productivity loss. Healthcare use is measured with the Medical Consumption Questionnaire from the Institute for Medical Technology Assessment (iMCQ), adjusted to fit our population [23]. The iMCQ includes questions related to frequently occurring contacts with healthcare providers. Healthcare costs are calculated by multiplying healthcare use by Dutch standard prices [24].

Productivity loss is measured with the Productivity Cost Questionnaire from the Institute for Medical Technology Assessment (iPCQ) [25]. The iPCQ consist of 12 items in three modules: lost productivity at paid work due to absenteeism, lost productivity at paid work due to presenteeism, and lost productivity at unpaid work. Productivity costs are calculated by multiplying productivity losses by standard Dutch age and sex-specific prices per hour [24].

3) Patients’ quality of life is measured with the EuroQol 5-Dimensions (EQ-5D-3 L). The EQ-5D-3 L consists of 6 items. Items 1–5 measure the health state on five dimensions (mobility, self-care, usual activities, pain/discomfort, and anxiety/depression). Each dimension has 3 levels: level 1 indicates no problems, level 2 indicates some problems, and level 3 indicates extreme problems. Item 6 measures the self-rated health on a vertical visual analogue scale (VAS) where the endpoints are labelled best imaginable health state (100) and worst imaginable health state (0). [26] There is evidence of construct validity and reliability for patients with knee injuries [27].

#### Secondary outcomes

1) Disability due to knee complaints is assessed with the Knee Injury and Osteoarthritis Outcome Score (KOOS) [28]. This questionnaire consist of 42 questions for five dimensions (pain, symptoms, function in daily living, function in sport and recreation, and knee-related quality of life). The answer options are standardised and rated on a scale from 0–4. The total score is calculated for each subscale on a scale from 0–100, a higher score indicating more symptoms. The KOOS has good validity, reliability, responsiveness, internal consistency and no floor or ceiling effect [28].

2) Severity of knee pain is assessed with the numeric rating scale (NRS). The NRS is an 11-point Likert scale, where 0 indicates no pain and 10 indicates unbearable pain. The NRS is a valid, reliable and appropriate rating scale for capturing severity of pain in clinical practice [29].

3) Patients’ perceived recovery is assessed with the Global Perceived Effect (GPE). The GPE is a 7-point Likert scale ranging from completely recovered to worse than ever [30]. The reliability of the GPE is excellent [31].

4) Patients’ satisfaction with the treatment is measured on a 7-point Likert scale ranging from absolutely satisfied to absolutely dissatisfied.

At baseline the following demographic data are collected: age, gender, height, weight, education level, co-morbidity, duration of complaints and previous knee complaints. Also collected are data on GPs’ initial working diagnosis, GPs’ preferred management at baseline, and MRI findings.

### Sample size calculation

The sample size is based on the Lysholm Scale. In our pilot study, at 1-year follow-up, the effect (Lysholm Scale) of usual care in general practice was estimated at a mean difference of −23 with a standard deviation of 17 (95% confidence interval; CI −27.8; −18.2) [12]. To obtain 80% statistical power with a 2-sided alpha of 0.05, 225 patients per treatment group are required to establish the non-inferiority of MRI referral by the GP compared with usual care within 4.8 points on the Lysholm Scale. Hence, using a 2-sided alpha of 0.05 and 225 patients per group, the trial has a 91% power to detect superiority of MRI referral over usual care assuming a clinically relevant difference of 15% in knee function. Based on previous studies we expect a loss to follow-up of 15%; therefore, the planned trial will require 520 patients with traumatic knee complaints [12,14].

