### Statistical analysis

Success of the randomisation and distribution of outcome measures will be checked before the actual analyses are performed. The baseline characteristics of the non-randomised patients in the cohort are analysed and compared with those of the randomised patients to gain insight into potential selection bias.

The economic evaluation is a cost-utility analysis from the societal perspective (costs per quality adjusted life-year; QALY), based on patients’ reports. A 1-year time horizon will be used, without discounting. Costs related to outcome are analysed using net-benefit acceptability curves, multiple imputation and bootstrapping, including only the uncertainty due to trial sampling error. Cost price analyses are performed for MRI and orthopaedic consultations. Other costs are valued using standard prices (including time involved and travel costs) [24]. QALYs are estimated as the area under the observed 1-year utility curves. Utilities are estimated using the EQ-5D-3 L (primary analysis, Dutch tariff) and the patients’ health VAS, transformed to a utility scale using the power transformation U = 1-(1-VAS/100)^1.61^.

We will evaluate whether MRI referral by GPs is non-inferior compared with usual care in accordance with the clinical guideline, beyond a specified non-inferiority margin (delta) with a defined confidence interval. Non-inferiority of MRI over usual care will be accepted if the upper bound of the 95% CI around the estimated difference in primary outcome (Lysholm Scale) lies below delta. A delta of 4.8 is adopted; this is based on the expected effect in the usual care group as found in our pilot study (see Sample size calculation), and on judgement about the difference between treatments that would be clinically meaningful.

The outcome of both groups are analysed on the basis of the ‘intention to treat’ principle. Linear mixed models with repeated measurements are used to calculate group differences over time. We will adjust for baseline variables that have a clinically meaningful difference between the two groups. In non-inferiority trials, because an intention to treat analysis can increase the type I error (i.e. the risk of falsely claiming non-inferiority), we will also perform a per-protocol analysis [32].

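### The stated inputs give 197 patients per group for 80% power, not 225; 225 gives about 85%, and 520 randomised with 15% loss leaves 221 per group (a conservative mismatch)

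*Protocol article*

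**What the plan says.** All the relevant figures are in the Protocol article.

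- **Size and power** (Sample size calculation): "To obtain 80% statistical power with a 2-sided alpha of 0.05, 225 patients per treatment group are required". The purpose is to "establish the non-inferiority of MRI referral by the GP compared with usual care within 4.8 points on the Lysholm Scale".
- **Variability** (same section): the one-year effect of usual care in the pilot study is "estimated at a mean difference of −23 with a standard deviation of 17". No other SD is given.
- **Second use of 225** (same section): the same number per group is said to give 91% power for superiority, for a clinically relevant difference of 15% in knee function.
- **Loss to follow-up** (same section): 15% is expected, and "therefore, the planned trial will require 520 patients with traumatic knee complaints". This allowance comes after the 225.
- **Margin and decision rule** (Statistical analysis): "A delta of 4.8 is adopted". The rule begins "Non-inferiority of MRI over usual care will be accepted if the upper bound of the 95% CI around the estimated difference in primary outcome" and requires that bound to lie below delta. A two-sided 95% interval corresponds to a one-sided test at 0.025, which agrees with the alpha in the sample size section.
- **Design** (Design): a "multi-centre, parallel group, open-labelled, non-inferiority randomised controlled trial (RCT) with a 1-year follow-up". Allocation uses blocks of 4 and 6, with the same number quoted for each group.

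The article states no assumed true difference, no allowance for clustering by centre or practice, and no other inflation of the 225.

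**The concern.** The paragraph prints the SD, margin, alpha, power and resulting size, so the size can be checked. It does not follow: 225 is about 14% above what the printed inputs require, too much for rounding. The step from 225 per group to 520 in total does not close either, because 520 less 15% is below the number called required.

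What is at stake is the record of the design power. Anyone who later weighs a recruitment shortfall or an inconclusive interval will ask what the trial was built to show and with how many evaluable patients. As printed, the paragraph gives a power that belongs to one size and a size that belongs to another power.

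**Working it through.** **Inputs.** From Sample size calculation: SD 17, margin 4.8, two-sided alpha 0.05 (one-sided 0.025), power 80%, 225 per group, loss 15%, total 520. The margin and the 95% interval are confirmed in Statistical analysis. My assumptions: the true difference is 0, allocation is 1:1, and the pilot SD of 17 applies to the between-group comparison.

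**1. Attempt to reproduce 225.**

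n per group = 2 × (z₀.₉₇₅ + z_power)² × SD² / margin²

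2 × 17² / 4.8² = 578 / 23.04 = 25.087

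- 80% power: (1.960 + 0.842)² = 7.849, and 7.849 × 25.087 = 196.9, so **197** (198 by the exact noncentral t calculation).
- 85% power: (1.960 + 1.036)² = 8.978, and 8.978 × 25.087 = 225.2, so 226.

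The printed 225 is not reproduced at 80% power. It is almost exactly the size for 85%. The excess is 28/197 = 14%.

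**2. Power at 225.**

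SE = 17 × √(2/225) = 1.603

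Power = Φ(4.8/1.603 − 1.960) = **0.850** (0.848 by noncentral t)

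**3. Alternatives at 80% power, SD 17 and margin 4.8 unless noted.**

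| Variant | n per group |
|---|---|
| One-sided alpha 0.05 | 156 |
| Equivalence (two one-sided tests), 0.05 each | 215 |
| Equivalence, 0.025 each | 264 |
| Most favourable rounding (SD 17.49, margin 4.75) | 213 |

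None gives 225.

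**4. What would give 225 at 80% power.**

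- A larger SD: √(225/2) × 4.8 / 2.802 = **18.2**.
- A smaller effective margin: 17 × √(2/225) × 2.802 = 4.49, that is, a true disadvantage of 4.80 − 4.49 = **0.31 points**.

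Neither value is stated.

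**5. The loss step.** This check needs no SD or assumed difference.

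- 520 × 0.85 / 2 = **221** per group, not 225.
- 450 / 0.85 = 529.4, so **530** randomised would be needed for 225 per group.
- 450 × 1.15 = 517.5, close to 520. The total is consistent with multiplying by 1.15 where division by 0.85 was needed.

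**6. Power at the number actually left.**

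SE = 17 × √(2/221) = 1.617

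Power = Φ(4.8/1.617 − 1.960) = **0.843**

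**7. The superiority figure that shares the 225.** At SD 17, 91% power with 225 per group corresponds to a difference of (1.960 + 1.341) × 1.603 = 5.29 points. At 221 per group the same difference gives Φ(5.29/1.617 − 1.960) = 0.905. The article does not say what the 15% is a percentage of. If it were 15% of the 23-point pilot effect, the difference would be 3.45 points, and power at 225 would be Φ(3.45/1.603 − 1.960) = 0.58.

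**The case against.** The strongest reply is that the article condenses a fuller protocol and does not fix every input. It states no true difference. It gives 17 as the SD of a within-group pilot effect without saying that this value was entered for the comparison of groups. A disadvantage of 0.31 points, an SD of 18.2, or a modest allowance for the multi-centre design would account for 225. This stands to the extent that the authors' calculation cannot be shown to be mistaken. It does not rescue the paragraph, which presents 225 as the consequence of inputs that do not produce it.

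The second reply is that nothing is lost: 225 exceeds 197, and even 221 exceeds it. This stands in full. The discrepancy between 221 and 225 alone moves the power only from 85.0% to 84.3%.

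Two stronger readings are tempting, and the documents support neither.

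- **The loss allowance was applied twice.** A reader might notice that 196 × 1.15 is about 225 and that 450 × 1.15 is about 520. But the requirement is 197, and 197 × 1.15 = 226.6. The text mentions loss only after 225, and a mislabelled 85% power fits at least as well. The article does not show where 225 came from.
- **The target could be cut.** Dividing 197 by 0.85 gives 232 per group, or 464 in total, and a reader might infer that 56 patients could be saved. But the article also claims 91% superiority power at 225 per group. For the 5.29-point difference implied at SD 17, power at 197 would be about 87%. Costs and quality of life are also primary outcomes, cost-effectiveness is the first listed objective, and a per-protocol analysis, which may use fewer patients, is planned. A reporting discrepancy is no ground for recruiting less.

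**Conclusion.** The point holds as an error of statement. On the printed inputs and a true difference of zero, 80% power needs 197 per group and 225 gives 85%. The total of 520 with 15% loss leaves 221 per group and 84% power, four per group short of the number called required. The first result rests on the zero difference and on SD 17 for the between-group comparison; the shortfall to 221 rests on the article's own figures alone.

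The direction is conservative. A reader might infer that the non-inferiority test is underpowered or its conclusion at risk. It is not: the stated 80% is exceeded on the stated inputs, and no error rate or decision rule changes. The weight is that of a sample size statement that should be made reproducible.

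**What to change.** Keep the target of 520 and restate the Sample size calculation in one of two ways:

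1. *520 randomised, with 15% loss to follow-up, leaves 221 evaluable patients per group and about 84% power to show non-inferiority within 4.8 Lysholm points (SD 17, true difference 0, two-sided alpha 0.05).*
2. If another input produced 225 at 80% power, state it (the SD used, the assumed true difference, or any other allowance). Then either describe 520 as leaving 221 evaluable per group, or show the 530 needed for 225.

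In either case, restate the superiority power for the same evaluable number, and say in Lysholm points what the 15% difference means.

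The cost is a rewording of one paragraph. The first option needs no extra patients and no change to the analysis.

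### The stated power and sample size do not match: with SD 17, margin 4.8 and two-sided alpha 0.05, 225 per group gives about 85% power, and 80% needs only 197 per group

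*Protocol article*

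**What the plan says.** The section *Sample size calculation* bases the trial on the Lysholm Scale. It takes its variability from the authors' pilot study of usual care, where the one-year change was estimated "with a standard deviation of 17". It then says: "To obtain 80% statistical power with a 2-sided alpha of 0.05, 225 patients per treatment group are required to establish the non-inferiority" of MRI referral against usual care, "within 4.8 points on the Lysholm Scale". A 15% loss to follow-up is applied after that, to reach 520 patients in total.

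The section *Statistical analysis* uses the same margin ("A delta of 4.8 is adopted") and gives the decision rule: non-inferiority is accepted if the "upper bound of the 95% CI around the estimated difference in primary outcome (Lysholm Scale) lies below delta". No other standard deviation, design effect, variance adjustment or assumed true difference appears in either section.

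**The concern.** The article prints a standard deviation, a margin, an alpha and a power, and then a number per group that it calls required. A reader can put the four inputs into the standard formula, and the result is not 225. This is not a detail left to a fuller document: the inputs and the result are both printed, and they disagree.

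This calculation sizes the trial for the second stated objective, non-inferiority on knee-related daily function. If 225 is read as the minimum for 80% power, ethics reviewers, funders and readers have a wrong figure for what the trial needs. It also misplaces the point at which attrition matters. With 260 randomised per arm, a floor of 225 is breached at a loss of 13.5%, which is less than the 15% the article itself expects. On the printed inputs the floor is 197, reached only at a loss of about 24%. A retention or extension decision taken against the printed figure would use the wrong threshold.

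**Working it through.** **Inputs**

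- Standard deviation: 17 (*Sample size calculation*; the only one given).
- Margin: 4.8 points (*Sample size calculation* and *Statistical analysis*).
- Alpha: 0.05 two-sided. One bound of a 95% CI is compared with the margin, so the non-inferiority test is at 0.025 one-sided, z = 1.960.
- Power: 80%, z = 0.842.
- Allocation: two equal groups of 225.
- True difference: not stated; taken as 0.

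**Number per group**

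n = 2 × (z₀.₉₇₅ + z_power)² × SD² / margin², with 2 × 17² / 4.8² = 578 / 23.04 = 25.09.

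| Power | (z₀.₉₇₅ + z_power)² | n per group |
|---|---|---|
| 80% | 7.849 | 196.9 |
| 85% | 8.978 | 225.2 |
| 90% | 10.507 | 263.6 |

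The plan's 225 is therefore not reproduced at 80%, where the answer is 197 (198 with the noncentral t). It is reproduced at 85%, apart from rounding up to 226. The excess over the 80% figure is 225 − 197 = 28 per group, and 28 / 197 = 14%.

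**Power at 225 per group**

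Standard error = 17 × √(2/225) = 1.603. Power = Φ(4.8 / 1.603 − 1.960) = Φ(1.035) = 0.850. The noncentral t gives 0.848.

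**Other readings of the test, at 80% power**

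| Reading | n per group |
|---|---|
| One-sided 0.05 | 156 |
| One-sided 0.0125 | 239 |
| Two-sided equivalence, 0.025 per side | 264 |
| Two-sided equivalence, 0.05 per side | 215 |

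None gives 225. Rounding of the SD does not explain it either: an SD of 17.49 gives 209.

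**What would give 225 at 80%**

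Changing one input at a time:

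- an SD of about 18.2;
- a margin of about 4.5 (4.49); or
- a true difference of about 0.3 points (0.31) against MRI.

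Separately, 197 × 1.15 = 227 is close to 225, so a 15% allowance may already have been included. The article, however, adds its allowance after 225: 450 × 1.15 = 518, close to 520.

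**Attrition**

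- 520 patients are 260 per arm. The share that can be lost before 80% power is reached is 1 − 197/260 = 24.2%.
- At the expected 15% loss, 260 × 0.85 = 221 per arm remain, and power is 0.843.
- Taking 225 as the floor instead: 1 − 225/260 = 13.5%.

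**The case against.** The strongest objection is that the printed inputs do not strictly rule out 225 at 80%, because the assumed true difference is never stated. A small disadvantage of 0.31 points for MRI, with all else unchanged, gives exactly that number. A loss allowance already inside 225 is another possible route. On this view the article has omitted an input and has not necessarily mis-stated the power, so 85% should not be presented as the proven origin of the figure. This stands as far as the cause is concerned: the document does not show how 225 arose. It does not rescue the sentence, because each of these routes needs an assumption that the article does not print.

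A second objection is that the harm is small. This largely stands. The discrepancy runs in the safe direction, no analysis or decision rule depends on 225, and the article ties no formal retention rule to it.

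A third is that 197 should not become a new safe floor. This also stands as a caution. The SD is a rounded pilot value, and a CI half-width of 4.8 implies only about 48 pilot patients: (1.96 × 17 / 4.8)² = 48.2. With an SD of 17.49 the requirement is 209, and the tolerable loss falls to 1 − 209/260, about 20%. With a true difference of 0.31 it falls to about 13%. The planned per-protocol analysis may also have fewer evaluable patients.

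**Conclusion.** The concern holds. On the stated SD, margin and alpha, and with a true difference of 0, 80% power needs 197 per group, and 225 per group gives 85.0% power (84.8% by noncentral t). The stated power is about 5 percentage points too low for the stated number or, put the other way, the stated number is 14% too high for the stated power. The trial is not underpowered on its own inputs. The fault is that its main sizing statement is wrong as written and cannot be reproduced. It should be corrected, but it does not threaten the design. The attrition figures rest on the SD being 17 and the true difference being 0.

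**What to change.** Replace the sentence with one that is true on its printed conditions: 225 patients per group give 85% power to establish non-inferiority within 4.8 points (SD 17, two-sided alpha 0.05, true difference 0); 80% power needs 197 per group.

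If 80% at 225 was really intended, print the input that produced it and use it throughout: an SD of about 18.2, a margin of about 4.5, or a true difference of about 0.3 points against MRI. If 225 already contained a loss allowance, say so and rework the step to 520. In every case state the assumed true difference.

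For the restated sentence the cost is one line of text. The recruitment target and the conduct of the trial stay as they are.
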